### Blinding and randomization

The randomization technique is stratified block randomization with varying sized blocks of 4, 6, 8 and 10 to prevent prediction of next assignment and to ensure sequence allocation concealment. Random sequence lists are stratified by age group (2–11 months and 12–59 months) to maintain similar composition of ages in both study arms. Separate randomization lists stratified by age (‘IN’ for infants 2–12 months of age and ‘CH’ for children 12–59 months of age) with drug labels (antibiotic or placebo) will be generated. This is done to reduce the chance that prescription errors will occur as investigators are using different weight bands for antibiotic dosages in these two age groups. Sequence generation was done at the AKU Clinical Trials Unit (CTU), electronically via computer using random selection method before the start of the study. This was done by an independent person unrelated to the trial.

This is a blinded study in which the drug assignment will be concealed from patients, parents, and study personnel. To ensure blinding, self-adhesive, pre-coded sticking labels with the unique identification numbers are prepared at the CTU and applied to the opaque medication bottles before providing to the study physicians. 4 digit randomization codes are used with two prefix characters for different age groups (e.g. IN0000, CH0000). Differentiation in code by age is to minimize chances of error in prescribing the wrong bottle. The codes will be kept safe with a person completely unrelated with the trial and broken only after analysis or upon the recommendation of the DSMB. This will ensure blinding of both the allocating physician as well as the one performing outcome assessment. Moreover, medication will be dispensed by community health workers who are not involved in treatment allocation and outcome assessment.

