### Statistical analysis

Baseline characteristics will be compared by analyzing differences in means and proportions among the study arms using the *chi-square* test for proportions and Student’s *t*-test for continuous variables. The primary analysis of outcomes will be a modified per protocol analysis comparing hazards of treatment failure with 95 % confidence intervals in the placebo arm with hazards in the amoxicillin arm. In order for an enrolled child to be included in the modified per protocol analysis, s/he must have received 5 out of 6 doses, including 4 doses in the first two days. Adjusted hazard rate ratios will be estimated accounting for the effect of any baseline variable found to differ between the two arms. Intention to treat analysis will also be performed for comparison.

Additionally, analyses will be done to identify predictors of treatment failure. Baseline characteristics between cumulative treatment success and failure groups by day 3 will be compared using the *chi square* test for categorical variables and Student’s *t*-test for continuous variables. A multivariate model will be constructed to look for determinants of cumulative treatment failure at day 3. All analysis will be done using STATA version 12. Sub-group analyses will be performed by age category, nasopharyngeal carriage, wheezing and initial fever.

Investigators propose to conduct one interim analysis using the O’Brien Fleming rule when 50 % per protocol subject accrual has been achieved. Termination will be done if p < 0.01 is observed with respect to the null hypothesis of inferiority. Final analysis will be done once enrollment is complete.

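### Covariates for the adjusted hazard ratio are to be picked by between-arm baseline tests, a rule that selects on imbalance and will almost never bring in the age stratum

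*Protocol article*

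**What the plan says.** Three statements in the protocol article bear on this.

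- **Baseline tests (Statistical analysis).** "Baseline characteristics will be compared by analyzing differences in means and proportions among the study arms", with the chi-square test for proportions and Student's t-test for continuous variables. No significance threshold and no list of variables is given.
- **Primary and adjusted analyses (Statistical analysis).** "The primary analysis of outcomes will be a modified per protocol analysis comparing hazards of treatment failure with 95 % confidence intervals". No covariate or stratum is named for it. The same paragraph then says: "Adjusted hazard rate ratios will be estimated accounting for the effect of any baseline variable found to differ between the two arms".
- **Randomisation (Blinding and randomization).** The method is "stratified block randomization with varying sized blocks of 4, 6, 8 and 10", and "Random sequence lists are stratified by age group (2–11 months and 12–59 months) to maintain similar composition of ages in both study arms". Age group is the only stratification factor named. A second purpose is given for the age-specific lists: "This is done to reduce the chance that prescription errors will occur".

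In the statistical analysis section, age category is named only as a subgroup variable. The non-inferiority margin of 2.5% (Hypothesis; Sample size) is an absolute difference in failure rates.

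**The concern.** A covariate earns its place in an adjusted analysis by predicting the outcome. A test of baseline balance between randomised arms says nothing about that. Among all randomised children, any difference such a test finds is chance, so the rule lets chance choose the model.

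Two consequences follow. First, the adjusted model is not defined until data by arm are examined, so nobody can say beforehand what the adjusted hazard ratio will be adjusted for. Secondly, the rule works against the one variable the design deliberately balances. Age group is kept even by blocking, so it will almost never be found to differ and will almost never enter, however strongly it may predict failure.

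The article does not say whether the unadjusted or the adjusted estimate decides non-inferiority. If both are available and one of them rests on a model chosen after the data are seen, a close result is open to dispute. The trial is meant to inform treatment guidelines, so that is worth avoiding.

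This is a stated rule and not a detail left to a later document. An analysis plan that fixed the covariates in advance would have to depart from it.

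**Working it through.** **1. The plan's sample size.** Inputs from the Sample size section: 5% failure in both arms, one-sided alpha 0.05, power 85%, margin 2.5 percentage points, 10% attrition.

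n per arm = (1.645 + 1.036)² × 2 × 0.05 × 0.95 / 0.025² ≈ 1093. Dividing by 0.90 gives 1215 per arm, or 2430 in total, which matches the stated figure. The calculation contains no covariate term, so fixing covariates in advance does not alter it.

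**2. Chance that a covariate enters by luck.** Assumptions, none of them in the article: a 0.05 threshold, k independent baseline variables, all randomised children. The chance of at least one apparent difference is 1 − 0.95^k.

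| k | chance |
|---|---|
| 5 | 23% |
| 10 | 40% |
| 15 | 54% |
| 20 | 64% |

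These are chances that the model is altered. They are not error rates for the non-inferiority decision.

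**3. Can age group be found to differ?** The largest block is 10, so an incomplete block leaves the arms at most 5 children apart in each age list. Assume 40% infants, so 972 infants and 1458 older children among 2430. In the worst case the two lists err in opposite directions:

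- infants 488.5 v 483.5, older children 726.5 v 731.5;
- difference in proportions 0.5026 − 0.4983 = 0.0043;
- standard error 0.5 × √(1/972 + 1/1458) = 0.0207;
- z = 0.21, p about 0.84.

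If each of the four sites ran its own lists (an assumption) and each left a block of 10 open, the gap could reach 20 per age group. Then 496/972 − 719/1458 = 0.5103 − 0.4931 = 0.0171, z = 0.83, p about 0.4. Neither case comes near 0.05.

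**4. What leaving age out costs in precision.** The documents give no failure rate by age, so the rates here are assumed. They average 5% with a 40:60 mix of infants to older children. The calculation is for the risk difference, the scale of the margin. Unstratified variance per child is 0.05 × 0.95 = 0.0475. Stratified variance is 0.4·p₁(1 − p₁) + 0.6·p₂(1 − p₂).

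| infants v older | stratified variance | variance ratio | SE ratio |
|---|---|---|---|
| 5% v 5% | 0.0475 | 1.000 | 1.000 |
| 6.5% v 4% | 0.04735 | 0.997 | 0.998 |
| 8% v 3% | 0.0469 | 0.987 | 0.994 |
| 11% v 1% (extreme) | 0.0451 | 0.949 | 0.974 |

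A simulation of 40,000 trials with about 1094 children per arm agrees, with standard-error ratios of 0.9995, 0.998, 0.993 and 0.974. Power for 8% v 3% is 0.850 unstratified and 0.853 stratified. In the extreme case it is 0.856 and 0.867.

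**The case against.** The strongest case against runs as follows.

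- **The adjusted ratio is secondary.** It follows the primary comparison and is not called primary. This stands, and it limits the harm. A reader might infer that chance-chosen covariates could carry the result across the margin. The documents do not support that: the only margin is a 2.5-point risk difference, the rule governs a hazard ratio, and no hazard-ratio margin is given.
- **Stratification keeps its value.** A reader might conclude that it is wasted. It is not. Both stated purposes, similar ages in the two arms and fewer prescription errors, are met whatever model is fitted.
- **Age is not certain to be left out.** The balance argument holds at randomisation. The primary set is modified per protocol (5 of 6 doses, 4 of them in the first two days) and is formed after randomisation, so age balance there is not assured. Age as a continuous variable could also differ within the wide 12–59 month stratum. The word 'guaranteed' would be wrong; 'almost never' is right.
- **Imbalance in that set may not be chance.** True, but this does not rescue the rule. A non-significant test does not exclude confounding, so the selected set needs prognostic covariates fixed in advance all the more.
- **Hazard ratios adjusted for different sets barely differ at 5% failure.** Also true. With assumed rates of 8% v 3% in a 40:60 mix, a conditional ratio of 1.50 corresponds to a marginal ratio of about 1.495.
- **Listing strata in the model is a matter for the analysis plan.** Silence about age alone would be no finding. Here, however, the article states how covariates are chosen, and that method selects on imbalance.
- **Age has not been shown to predict failure.** Fair. It sets the respiratory-rate cut-off for entry and the dosing band, which makes it a natural candidate and no more.

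**Conclusion.** The point holds as a modest one. The article fixes a poor selection rule: covariates enter the adjusted hazard ratio because the arms happen to differ, the model is unknown until data by arm are seen, and the only randomisation stratum will almost never qualify.

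The main defect is data-driven selection. With 5 to 15 independent variables tested at 5%, the chance that luck alone puts something into the model is 23% to 54%. Both the threshold and the number of variables are assumptions.

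Lost precision is a minor matter. Ignoring age group makes the standard error of the risk difference about 0–1% too large under moderate assumed age effects and under 3% too large in an extreme one. The error is slightly conservative. No conclusion about bias in the primary comparison, or about a changed non-inferiority decision, can be drawn from this rule.

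**What to change.** In the statistical analysis section:

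1. Delete the rule that adjusts for whatever is found to differ, and do not use between-arm baseline tests to choose covariates.
2. Stratify or adjust the primary comparison by randomised age group (2–11 v 12–59 months).
3. If a further adjusted analysis is wanted, fix its covariates now from baseline data already collected, for example site, wheeze and initial fever.
4. State which estimate decides non-inferiority, and label the others as supporting.

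This is a change of wording only. It needs no new data and leaves the sample size at 2430. It should be made before anyone sees outcome data by arm.

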### Hypothesis

The null hypothesis for this trial is that the absolute treatment failure rate of children 2–59 months of age presenting at a primary healthcare (PHC) facility for treatment of WHO defined fast breathing pneumonia who receive 3 days of placebo is worse than 3 days of amoxicillin by 2.5 % (TF_placebo_—TF_amoxicillin_ > 2.5 %, assuming TF of 5 % in amoxicillin group).

The alternate hypothesis is that absolute treatment failure rate of children 2–59 months of age presenting at a primary healthcare (PHC) facility for treatment of WHO defined fast breathing pneumonia who receive 3 days of placebo is equal to or not worse than 3 days of amoxicillin by 2.5 % (TF_placebo_—TF_amoxicillin_ ≤ 2.5 % assuming TF of 5 % in amoxicillin group).

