## Methods

### Design

This is a randomized double blinded placebo-controlled non-inferiority trial with parallel assignment and treatment allocation ratio of 1:1.

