### Sample size

In the study of Hazir et al [28], cumulative TF rates at day 3 were reported to be between 4 % and 7 % in tertiary level hospital setting. Given that the currently described study is conducted in a primary care setting, investigators have estimated that the TF rate of 5 %. Assuming a TF rate of 5 % in both the arms, using one sided alpha of 0.05, power of 85 %, non-inferiority margin of 2.5 % and an expected 10 % lost to follow-up/non per protocol, the minimum total estimated sample size required is 2430. Placebo will be judged to be “no worse” than amoxicillin if the lower bound of the 95 % confidence interval lies in the allowed margin.

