**Fig. 3 Fig3:**
[figure not shown]
Framework to ensure patient safety in the study

A trial steering committee, including international experts appointed by study sponsors, provides overall supervision of the safety and wellbeing of participants and ensures adherence to standards of the Medical Research Council. An independent Data Safety Monitoring Board (DSMB) has been formed to monitor safety of study participants, providing study oversight by un-blinded monitoring of study results to ensure safety of participants. If a safety signal is observed, the DSMB may stop this study prior to full recruitment. It is possible that placebo and amoxicillin are not similar in the management of fast breathing pneumonia and that the participants receiving placebo suffer a higher failure rate. Investigators believe that the existence of safety net will minimize the chances of harm to participants.

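### The interim threshold p < 0.01 has no stated side and matches no O'Brien-Fleming boundary at half accrual, and the final level is not adjusted for the look; the effect on error is small.

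*Protocol article*

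**What the plan says.** The design is a "non-inferiority trial with parallel assignment and treatment allocation ratio of 1:1". Under Hypothesis, the null is that "3 days of placebo is worse than 3 days of amoxicillin" by more than 2.5 percentage points, so rejecting it establishes non-inferiority.

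The Sample size section is explicit about its inputs: "Assuming a TF rate of 5 % in both the arms", "using one sided alpha of 0.05", 85% power, a "non-inferiority margin of 2.5" percentage points and 10% loss, giving 2430 children. It then judges the final result by whether a bound of the 95% confidence interval lies within the margin. It does not say whether that interval is one-sided or two-sided.

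The Statistical analysis section reads "Investigators propose to conduct one interim analysis using the" O'Brien-Fleming rule, at 50% of per-protocol accrual. The trial stops if p < 0.01 "is observed with respect to the null hypothesis of inferiority. Final analysis will be done once enrollment is complete". No side is given for p and no significance level for the final analysis.

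For harm, the Patient safety section says "It is possible that placebo and amoxicillin are not similar in the management of fast breathing pneumonia" and that children on placebo may fail more often. It gives an independent, unblinded DSMB the power to stop on a safety signal.

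**The concern.** An O'Brien-Fleming design with one interim look is a pair of thresholds, one for the interim and one for the end, which together use the overall alpha. Here the rule is named, but the one number given is not its interim value, and the criterion given for the end is the one a trial with no interim look would use. A DSMB could not tell whether the named rule or the printed number governs, nor on which side p is to be read.

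What is at stake is the false non-inferiority rate: the chance of declaring placebo acceptable when it is truly 2.5 points worse. The Conclusion says that a non-inferior result may support a change in treatment guidelines, so this rate should be the one declared.

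**Working it through.** **The plan's own figure.** Inputs from the Sample size section: 5% failure in both arms, margin 0.025, one-sided alpha 0.05, power 85%, loss 10%.

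- n per arm = (1.645 + 1.036)² × 2 × 0.05 × 0.95 / 0.025² ≈ 1093.
- 1093 / 0.90 = 1214.4, rounded up to 1215 per arm, 2430 in total. This matches exactly.
- At one-sided 0.025 the same steps give 3034, which does not match.

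The declared overall alpha is therefore one-sided 0.05, and all of it is used in the sizing, with nothing set aside for the interim.

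**Boundaries.** With one look at 50% information, the interim and final statistics are bivariate normal with correlation √0.5 = 0.707. Classical O'Brien-Fleming takes z₁ = C√2 and z₂ = C, with C solved so that P(Z₁ > z₁ or Z₂ > z₂) equals alpha under the null. For alpha 0.05, C = 1.678, so z₁ = 2.373. One-sided levels:

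| Overall one-sided alpha | Version | Interim p | Final p |
|---|---|---|---|
| 0.05 (declared) | Classical | 0.0088 | 0.0467 |
| 0.05 (declared) | Lan-DeMets type | 0.0056 | 0.0482 |
| 0.025 (comparison only) | Classical | 0.0026 | 0.0240 |
| 0.025 (comparison only) | Lan-DeMets type | 0.0015 | 0.0245 |

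None is 0.01. The nearest is 0.0088, which becomes 0.01 only when rounded up.

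**Overall error of the rule as written**, P(Z₁ > z₁ or Z₂ > z₂), for each reading of the two unstated sides:

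| Interim p < 0.01 read as | Final one-sided 0.05 | Final two-sided 95% interval (one-sided 0.025) |
|---|---|---|
| One-sided | 5.4% | 3.0% |
| Two-sided (0.005 one-sided) | 5.15% | 2.7% |

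Every cell exceeds the level of its own final test. Only the left-hand column exceeds the declared 5%.

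**Which part causes the excess.** With a final level of 0.05, the exact interim value 0.0088 gives 5.32% and 0.01 gives 5.37%. The rounding adds about 0.05 points, and the rest comes from leaving the final level unadjusted. Keeping interim one-sided 0.01 and holding 5% overall requires a final level of 0.0460.

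**Chance of stopping early.** Half of 1093 is about 547 per arm. The standard error is √(2 × 0.05 × 0.95 / 546.5) = 0.01318, so with 5% in both arms the expected interim z is 0.025 / 0.01318 = 1.896.

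- At p < 0.01: Φ(1.896 − 2.326) = 33%.
- At p < 0.0088: Φ(1.896 − 2.373) = 32%.

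**Power of a repaired rule**, fixed-sample with 1093 per arm: 85.0% at final 0.05, 84.2% at 0.0467, 84.1% at 0.0460. These ignore the added chance of crossing at the interim, so they slightly overstate the loss.

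**The case against.** The strongest reply is that 0.01 is the classical 0.0088 rounded to two decimals, that naming O'Brien-Fleming already implies an adjusted final level, and that a journal article may leave the exact final level to an analysis plan or DSMB charter not shown here. Much of this stands. The rounding is almost harmless, and if p < 0.01 is two-sided the interim is stricter than the classical boundary. The reply does not remove the point, because the article is not silent: it prints an interim number that differs from the rule it names, and it prints a final criterion, a 95% interval, on a sample size that uses the whole 0.05.

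A reader might go further in two ways that the document does not support.

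- **Comparing 0.01 with 0.0026.** This makes the mismatch look fourfold and the early-stop chance 33% against 18%. But 0.0026 belongs to overall one-sided 0.025, which the protocol does not declare. At the declared alpha the comparison is 33% against 32%. Adopting the 0.0026/0.0240 pair would also cut power to about 76% at the planned size.
- **Reading the plan as having no protection against harm on placebo.** By the Hypothesis section, the only numerical rule does stop for non-inferiority. But the Patient safety section gives an unblinded DSMB authority to stop for safety, and a numerical harm guideline is ordinary charter content. Its absence from an article is not an error.

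**Conclusion.** The point holds in a limited form. The printed interim threshold is not the O'Brien-Fleming value for the declared alpha, its side is not stated, and the stated final criterion makes no allowance for the look. With a final one-sided 0.05 test, the overall false non-inferiority rate is 5.4% (5.15% if the interim p is two-sided) against a declared 5%. With a final two-sided 95% interval it is 3.0%, which stays within the declared 5%. An unconditional claim that the declared error rate is exceeded is therefore not justified.

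These figures assume one look at exactly half the information, normal test statistics, a binding stop when the boundary is crossed and, for the stopping and power figures, 5% failure in both arms. An analysis plan not shown may already set the final level, in which case the article's wording needs to agree with it. The defect is small but concerns a decision threshold, and it is cheap to correct.

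**What to change.** State that the interim p is one-sided and choose one of these:

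- Replace p < 0.01 by 0.0088 at the interim and 0.0467 at the end. The final interval is then one-sided 95.3%, or two-sided at 1 − 2 × 0.0467 ≈ 90.7%. Fixed-sample power goes from 85.0% to about 84.2%.
- Keep 0.01 at the interim and set the final one-sided level at 0.0460, with the interval to match. Power is about 84.1%.
- Drop the non-inferiority stop. No alpha is then spent and the final criterion needs no adjustment for the look. The cost is losing the option to finish early for non-inferiority.

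In the first two cases, say in the Statistical analysis section that crossing the boundary means stopping because non-inferiority has been shown. In every case, say there that stopping for harm on placebo rests with the DSMB as described under Patient safety. Only wording changes, in the protocol and in any analysis plan or charter that repeats the rule. The planned 2430 can stay if a loss of under one point of power is accepted.

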### Ethical considerations

#### Ethical approval and consent

The study received ethical approval by the Ethics Review Committee of Aga Khan University (ERC reference number 2786-Ped-ERC-13). An ethical opinion was also sought from the Faculty of Medicine Ethics Committee at Southampton University, UK. A written informed consent is sought by an independent physician from the caretakers of all eligible children for participation in the study. All study procedures abide by the approved protocols.

#### Patient safety

All children enrolled in the trial are closely monitored for deterioration or development of new clinical signs. Children who are sick but not enrolled are followed for safety and ethical reasons, but will not be included in study analyses or reporting. There are several safety nets to ensure that there is quick identification of both early as well as late deterioration with immediate referral and treatment (Fig. 3).

